# The effectiveness of percutaneous endoscopic decompression compared with open decompression and fusion for lumbar spinal stenosis: protocol for a multicenter, prospective, cohort study

**DOI:** 10.1186/s12891-022-05440-4

**Published:** 2022-05-27

**Keywords:** Lumbar spinal stenosis, Percutaneous endoscopic decompression, Open decompression and fusion, Comparative effectiveness

## Abstract

**Background:**

Lumbar spinal stenosis (LSS) is one of the most frequent indications for spine surgery. Open decompression and fusion surgery was the most common treatment and used to be regarded as the golden standard treatment for LSS. In recent years, percutaneous endoscopic decompression surgery was also used for LSS. However, the effectiveness and safety of percutaneous endoscopic decompression in the treatment of LSS have not been supported by high-level evidence. Our aim is to 1) compare the effectiveness of percutaneous endoscopic decompression surgery and open decompression and fusion for the treatment of LSS. 2) Investigate the prognosis risk factors for LSS. 3) Evaluate the influence of percutaneous endoscopic decompression for the stability of operative level, and degeneration of adjacent level.

**Methods:**

It’s a prospective, multicenter cohort study. The study is performed at 4 centers in Beijing. This study plans to enroll 600 LSS patients (300 patients in the percutaneous endoscopic decompression group, and 300 patients in the open decompression and fusion group). The demographic variables, healthcare variables, symptom related variables, clinical assessment (Visual analogue score (VAS), Oswestry disability index (ODI), Japanese Orthopaedic Association score (JOA)), and radiological assessment (dynamic X-ray, CT, MRI) will be collected at baseline visit. Patients will follow up at 3, 6, 12 months. The primary outcome is the difference of improvement of ODI between baseline and 12-month follow-up between the two groups. The secondary outcome is the score changes of preoperative and postoperative VAS, the recovery rate of JOA, MacNab criteria, patient satisfaction, degeneration grade of adjacent level, ROM of operative level and adjacent level, complication rate.

**Discussion:**

In this study, we propose to conduct a prospective registry study to address the major controversies of LSS decompression under percutaneous spinal endoscopy, and investigate the clinical efficacy and safety of percutaneous endoscopic decompression and open decompression in the treatment of LSS.

**Trial registration:**

This study has been registered on clinicaltrials.gov in January 15, 2020 (NCT04254757). (SPIRIT 2a).

## Background

Lumbar spinal stenosis (LSS) is caused by the degeneration of the lumbar spine including disc herniation, the hypertrophy of facet joint and ligamentum flavum, and the formation of osteophyte [1]. The characteristics of LSS are low back pain, sciatica, and intermittent claudication which will seriously affect the daily life and work of patients [1, 2].

LSS is the most frequent indication for spine surgery among the elderly population [3, 4], and previous studies have demonstrated that surgical treatment was better than conservative treatment in selected patients [5, 6].

Open decompression and fusion was the most common treatment and used to be regarded as the golden standard treatment for LSS [7, 8]. However, due to the surgical trauma caused by open decompression and fusion surgery, complications, and the acceleration of adjacent level degradation, more minimally invasive treatments were required [9–11].

Percutaneous endoscopic decompression is a minimally invasive treatment which has the advantage of operated under local anesthesia, less surgical trauma, fewer complications, shorter hospital stay, and rapid postoperative recovery. The application of percutaneous endoscopic decompression has been limited to soft disc herniation. In recent years, with the development of endoscopic instruments and surgical techniques, some surgeons applied percutaneous endoscopic decompression for the treatment of LSS [12–14]. However, the related studies had some limitations including small sample size, short-term follow-up, single-center, no control group, retrospective study which reduced the quality of evidence for the conclusion. (SPIRIT 6a,b).

The present prospective, multicenter, large sample size cohort study based on real-world will be helpful for the evaluation of the clinical effectiveness and safety of the percutaneous endoscopic decompression for LSS. Furthermore, we designed to analyze various influence factors for the prognosis of LSS including degeneration grade, pathology type, stenosis grade, decompression range. The present study will provide useful information for the development of guidelines and standards for percutaneous endoscopic decompression for the treatment of LSS.

## Methods

### Aim and objective

The primary aim of this study is to compare the effectiveness and safety of percutaneous endoscopic decompression surgery and open decompression and fusion surgery for the treatment of patients with LSS in the real-world treatment setting. The secondary aim is to investigate the prognosis factors for LSS treated by surgery.

The objectives of this study:Compare the clinical outcomes of percutaneous endoscopic decompression and open decompression and fusion for lumbar spinal stenosis.Investigate the influence of various factors (including demographic variables, risk factors, treatment factors, and radiological assessment) for the clinical outcome of LSS treated by surgery.Investigate the influence of percutaneous endoscopic decompression surgery on stability of the operated level.Investigate the influence of percutaneous endoscopic decompression surgery on degeneration of adjacent level. (SPIRIT 7)

### Study design

The present study is a multicenter, prospective, cohort study that will compare the effectiveness of percutaneous endoscopic decompression surgery and open decompression and fusion surgery for lumbar spinal stenosis in the real-world treatment setting. The study will enroll 600 patients (300 patients in the percutaneous endoscopic decompression group, and 300 patients in the open decompression and fusion group) from 11 June 2020 to 31 December 2022. The patient will be followed up at 3, 6, and 12 months postoperatively. The study is due to be completed on 31 December 2022. (SPIRIT 8).

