### Sample size calculation

The sample size calculation was based on the ODI score at 12 months follow-up. According to the retrospective study of our center and previous literature reported [15], the mean value and standard deviation of ODI score in 12 months after surgery was 20 and 15 in the percutaneous endoscopic decompression group, and 15 and 10 in the open decompression and fusion group. Assuming an overall type 1 error (α) of 0.05 and type II error (β) of 0.1, we needed 137 patients in each group to detect the difference of ODI in two groups. Considering the final follow-up rate of 80% and the center effect value of 1.2, a minimum of 206 patients were needed in each group. Moreover, this study is a real-world observation study, it is necessary to consider confounding factors when analyzing the results. We estimated that 300 patients in each group will be enrolled in this study. (SPIRIT 14).

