### Outcome measures

#### Primary outcome measure

The primary outcome measure is the score changes of ODI between baseline and 12-month follow-up.

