### Missing data

At the final complete analysis for the primary outcome, we will exclude the cases which missing ODI data at 12 months follow-up [26]. Missing data could influence the validity of prospective studies, we will aim to maximize the follow-up rate to above 80%. (SPIRIT 20c).

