### Trial status

The protocol was the second version (V2, 2020/06/30). The protocol status was in recruiting status and have not completed, in which the recruitment began on 11 June 2020 and it will be completed on 31 December 2022. (SPIRIT 3).

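### Enrolment and study completion share one end date, 31 December 2022, which cannot be squared with a primary outcome measured 12 months after surgery

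*Protocol article*

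**What the plan says.** The Study design section of the protocol article sets the enrolment of 600 patients, 300 per group, in the period "from 11 June 2020 to 31 December 2022". It then sets the visits: "The patient will be followed up at 3, 6, and 12 months postoperatively". It closes with the end date: "The study is due to be completed on 31 December 2022".

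The Primary outcome measure section fixes the time point: "The primary outcome measure is the score changes of ODI between baseline and 12-month follow-up". The Missing data section says of the primary analysis that "we will exclude the cases which missing ODI data at 12 months follow-up", and aims for follow-up above 80%.

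The Trial status section gives the same date again: "the recruitment began on 11 June 2020 and it will be completed on 31 December 2022". No section gives a later end of follow-up or an earlier last-enrolment date.

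**The concern.** Three statements conflict: enrolment runs to the end of 2022, every patient is followed for 12 months after surgery, and the study ends on the same day as enrolment. At least one must be wrong, whatever the accrual pattern.

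What is at stake is the availability of the primary endpoint. If the dates were applied literally, patients from the last year of enrolment would lack a 12-month ODI for calendar reasons alone, and the complete-case rule would take them out of the primary analysis. The 12-month imaging outcomes would be cut off in the same way. The 80% follow-up rate in the Sample size calculation makes no stated allowance for such a cut. The margin between 206 and 300 per group, which the article reserves for confounding, would be the first thing lost.

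**Working it through.** **Inputs.** Enrolment window, completion date and 300 per group: Study design. From Sample size calculation: mean and SD of 12-month ODI, which "was 20 and 15 in the percutaneous endoscopic decompression group" and 15 and 10 in the open group (difference 5); α = 0.05; β = 0.1; follow-up rate 80%; center effect 1.2. Sidedness of α is not stated. Accrual is not stated.

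**Step 1. Reproduce the plan's own figures.** n per group = (15² + 10²) × (1.960 + 1.282)² / 5² = 136.6, rounded up to 137. This matches with a two-sided test; a one-sided test gives 112 and does not match. Inflation: 137 × 1.2 / 0.80 = 205.5, rounded up to 206. Both stated figures reproduce, so the same inputs can be used below.

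**Step 2. Dates.** 11 June 2020 to 31 December 2022 is 933 days. The last surgery date that allows a 12-month visit by 31 December 2022 is 31 December 2021, day 568. The remaining 365 days are 365/933 = 39.1% of the window. This step needs no assumption about accrual.

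**Step 3. Patients affected, under two assumptions.** Assume that 31 December 2022 is the data cut-off and that accrual is uniform, with the enrolment date taken as the surgery date. Then 600 × 0.391 ≈ 235 patients cannot reach 12 months. About 365 can, or 300 × 0.609 ≈ 183 per group. At most 61% have 12-month data before any ordinary loss.

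**Step 4. Power.** With m patients per group who can reach 12 months, the effective number is n = m × 0.8 / 1.2, and power = Φ(5 / √(325/n) − 1.96).

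- Uniform accrual: 183 × 0.8 ≈ 146 evaluable per group (0.609 × 0.8 ≈ 49% of those enrolled), against 240 implied by 300 × 0.8 and about 164 needed (137 × 1.2). n = 121.8 and power = Φ(1.10) ≈ 86%.
- Same accrual, but with no loss beyond the cut-off: n = 183/1.2 ≈ 152 and power = Φ(1.46) ≈ 93%.

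**Step 5. Range over accrual, with the further 20% loss.**

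| Share operated on by 31 Dec 2021 | Per group able to reach 12 months | After 20% loss | Divided by 1.2 | Power |
|---|---|---|---|---|
| 40% | 120 | 96 | 80 | 70% |
| 50% | 150 | 120 | 100 | 79% |
| 60.9% (uniform) | 183 | 146 | 122 | 86% |
| 70% | 210 | 168 | 140 | 91% |
| 80% | 240 | 192 | 160 | 94% |
| 100% (no cut-off) | 300 | 240 | 200 | 97.5% |

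To keep the article's own minimum of 206 per group, 206/300 = 69% must be operated on by 31 December 2021.

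**The case against.** The strongest reply is that the loss of patients is inferred, not planned. No section calls 31 December 2022 a data cut-off. The Quality control section locks the database after the study is completed and the data are checked, without a calendar date. The Missing data section does not say that patients not yet due at 12 months count as missing. One date may simply be a slip: the window may have been meant for the whole study, or completion may be a year later. This stands as far as it goes. A reader might infer that the plan intends to drop 39% of the cohort; the text does not support that. It also does not say which date is wrong, so the conflict remains under either explanation.

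A reader might also infer that the 80% follow-up target and the planned power are out of reach. That is too firm. It rests on the cut-off and on accrual: with 70% or more operated on by the end of 2021, power stays above 90%. Falling below 90% under uniform accrual also depends on taking the 20% loss on top of the cut-off, and the article does not say whether its 80% covers all causes.

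The Trial status section is weaker support than it looks. Its pronoun may refer to recruitment or to the study, so it does not settle which event the date belongs to.

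Finally, it is tempting to add that late patients are those treated with the most endoscopic experience, so that losing them would bias the comparison. The article records the surgeon but describes no rise in experience during the study, so this has no support here.

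**Conclusion.** The point holds as an internal contradiction. Enrolment to 31 December 2022, 12 months of follow-up and completion on 31 December 2022 cannot all be true, and no other section resolves it. This conclusion needs no assumption.

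The size is conditional. It requires the completion date to act as the data cut-off, and it depends on accrual. Under uniform accrual, the sample falls short of the article's own requirement and power drops a few points below target if ordinary loss comes on top. Over the accrual patterns examined the result runs from a serious loss of power to none below the target. The scenario shows what follows if the dates are applied literally; it does not forecast what the study will do.

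**What to change.** State two separate dates in Study design: last enrolment and study completion. With enrolment open to 31 December 2022, set completion and the data cut-off for the primary analysis after the last patient's 12-month visit, which is not before about 31 December 2023. Reword Trial status so that its date names the event it belongs to.

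Closing enrolment by 31 December 2021 would also reconcile the dates on paper. It is hardly practical for an article published on 27 May 2022 that describes recruitment as ongoing.

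The cost is a correction to the dates and about 12 more months of follow-up that the article already promises each patient. No extra patients are needed. The registry record was not available, so whether its dates need the same change should be checked and not presumed.

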### Sample size calculation

The sample size calculation was based on the ODI score at 12 months follow-up. According to the retrospective study of our center and previous literature reported [15], the mean value and standard deviation of ODI score in 12 months after surgery was 20 and 15 in the percutaneous endoscopic decompression group, and 15 and 10 in the open decompression and fusion group. Assuming an overall type 1 error (α) of 0.05 and type II error (β) of 0.1, we needed 137 patients in each group to detect the difference of ODI in two groups. Considering the final follow-up rate of 80% and the center effect value of 1.2, a minimum of 206 patients were needed in each group. Moreover, this study is a real-world observation study, it is necessary to consider confounding factors when analyzing the results. We estimated that 300 patients in each group will be enrolled in this study. (SPIRIT 14).

### Study population and enrollment

The target population of this study was patients diagnosed with LSS who failed of conservative treatment and prepared for surgical treatment. The study is performed at Peking University Third Hospital, Beijing Shijitan Hospital of capital medical university, Xuanwu Hospital of capital medical university, and Beijing Changping Hospital. Potential participants will be screened by experienced orthopaedic surgeons or neurosurgeons at each clinical center. Patients met the eligibility criteria will be offered the detailed description of all alternative treatment. After careful consideration, patients will be asked to select their preferred treatment approach. When patients decide upon their treatment option, the physicians will explain this protocol and informed consent to participate will be obtained. All procedures of the study, and the rights, responsibilities, benefits, risks of the participant will be completely informed, and the informed consent form will be signed. Flow chart of the study design is shown in Fig. 1. (SPIRIT 9, 15).

**Fig. 1 Fig1:**
[figure not shown]
Flow chart of the study. VAS, Visual analogue score (VAS); ODI, Oswestry disability index; JOA, Japanese Orthopaedic Association score. X-ray including anterior-posterior position, lateral position, flexion and extension position lumbar X-ray

### Eligibility criteria

#### Inclusion criteria

Older than 18 years.Diagnosed with lumbar spinal stenosis.Responsibility level was <= 2.Patients with adjacent segmental stenosis or stenosis at operation level after lumbar surgery.Symptoms with no relief by conservative management for at least 6 weeks.Patients agree to participate in the study and willing to complete the follow-up.

#### Exclusion criteria

Symptoms were only caused by lumbar disc herniation.Instability at responsibility level.Isthmic Lumbar Spondylolisthesis or degenerative lumbar spondylolisthesis was greater I degree.Conditions affect the lumbar spine (infection, tumor, and neurological diseases, etc.) (SPIRIT 10)

### Treatment

#### Percutaneous endoscopic decompression group

##### Transforaminal approach

Patients were placed in a lateral position. The surgery was performed under local anesthesia (1% Ropivacaine 10 ml, 2% Lidocaine 15 ml, 0.9% Normal Saline 20 ml). After confirmed the entry point and the direction of approach, an 18-guage spinal needle was inserted to the surface of the superior articular process by the guidance of fluoroscopy. Insert a guidewire to replace the spinal needle, and then a series obturator was inserted through the guidewire. Finally, a working cannula was inserted through the obturator. After the location of the cannula was confirmed by fluoroscopy, the endoscope system and endoscopic trephine were inserted. The foramen, lateral recesses, and the posterior of the vertebral body could be decompressed by the transforaminal approach.

##### Interlaminar approach

Patients were placed in a prone position. The surgery was performed under 5μg Sufentanil intravenously and local anesthesia (1% Ropivacaine 10 ml, 2% Lidocaine 15 ml, 0.9% Normal Saline 20 ml). Inserted an 18-guage spinal needle to the posterior of ligamentum flavum, and confirmed the needle is located at the midpoint of the interlaminar space by the fluoroscope. Inserted the guidewire, obturator, working cannula, endoscopic trephine, and the endoscope system in sequence. The foramen, lateral recesses, and central canal could be decompressed by the interlaminar approach. The unilateral decompression or bilateral decompression could be chosen depending on the stenosis.

All decompression procedures of both approaches were performed under the observation of the endoscopic view. The decompression was completed when compressed dura and nerve root could be seen, and the nerve root could be mobilized freely by a flexible probe.

#### Open decompression and fusion group

Patients were placed in a prone position. The surgery was performed under general anesthesia. After exposed to the lamina, inserted the pedicle screw. The posterior decompression including laminectomy, lateral recesses resection, and foraminotomy was performed according to the stenosis. Interbody fusion or posterolateral fusion is determined by the surgeon’s preference.

‘X’ indicates that the procedure is carried out.

VAS, Visual analogue score (VAS); ODI, Oswestry disability index; JOA, Japanese Orthopaedic Association score. X-ray including anterior-posterior position, lateral position, flexion and extension position lumbar X-ray.

### Follow up

Patients will be followed up at 3, 6, 12 months after surgery. Clinical and radiological assessment at 3 and 12 months after surgery will be performed through outpatient follow-up. Clinical assessment at 6 months after surgery will be completed through email or telephone (Table 1). Adverse events will be recorded during the follow-up period. (SPIRIT 13, 18b).

**Table 1 Tab1:** Data collection

Variables	Baseline	Perioperative	3 months	6 months	12 months
Demographic Variable					
Age	X				
Gender	X				
BMI	X				
Ethnicity	X				
Center of residence	X				
Risk Factors					
Comorbidity	X				
Smoking status	X				
Previous spinal surgery	X				
Pathology types	X				
Affected level	X				
Symptoms duration	X				
Degeneration grade	X				
Stenosis grade	X				
Treatment Factors					
Operation approach		X			
Operative time		X			
Bleed loss		X			
Postoperative hospital stay		X			
Surgeon		X			
Radiological Assessment					
X-ray	X		X		X
CT	X		X		X
MRI	X		X		X
Clinical Assessment					
VAS (back & leg)	X	X	X	X	X
ODI	X		X	X	X
JOA	X		X	X	X
MacNab criteria			X	X	X
Patient satisfaction		X	X	X	X
Complications		X	X	X	X

### Measures

#### Exposure measures

The exposure measures include demographic variables, risk factors and treatment factors. The demographic variables included age, gender, BMI, ethnicity, and center of residence. The risk factors were composed of healthcare variables (Comorbidity, smoking status, previous spinal surgery), and symptom related variables (Pathology types, affected level, symptoms duration, degeneration grade, stenosis grade). The treatment factors included operation approach, operative time, bleed loss, postoperative hospital stay, surgeon. The demographic variables, and risk factors were collected after patients were enrolled in the study, and before the surgery was performed. The treatment factors were collected before patients were discharged. (Table 1).

#### Special measures

The special measures were composed of clinical assessment and radiological assessment.

### Clinical assessment

Visual analogue score (VAS) [16], Oswestry disability index (ODI) [17], Japanese Orthopaedic Association score (JOA) [18], MacNab criteria, Patient satisfaction, Complications.

VAS divided the degree of pain from 0 to 10. 0 represented no pain, and 10 represented the most pain. VAS was used to evaluate the pain of the back and lower limb separately.

ODI was wildly used to evaluate the limitations of daily activities caused by spinal diseases. The simplified Chinese version ODI was composed of 10 questions, including pain intensity, self-care, lifting, walking, sitting, standing, sleep, sex, social, travel. The score range for each question was 0–5 points. Summarized each question patient answered and converted into a percentage score.

JOA was an effective method to assess lumbar diseases and the recovery of lumbar spine surgery. The simplified Chinese version JOA included five aspects: low back pain (four items), lumbar function (six items), walking ability (five items), social life function (four items), and mental health (seven items). The recovery rate was calculated according to preoperative and postoperative JOA.

MacNab criteria were used to access the overall effectiveness of the surgery, including four grades: excellent, good, fair, poor.

Patient satisfaction was the patient’s subjective impression of surgery, including three grades: satisfied and accept, not satisfied but accept, not satisfied, and not accept.

